### Intervention arm (NP-led care arm)

Participants randomized to the intervention group will be contacted by the NP to be scheduled for an appointment with the NP within 4 to 6 weeks from the date of the referral. The NP consultation will include patient history, physical examination, symptomatic management strategies as appropriate (e.g. bladder and bowel management strategies, fatigue management, depression, anxiety, spasticity), discussion of mental and physical health resources for symptomatic treatment, support, physical and mental health resources to optimize functioning (e.g. home care or physical/occupational therapy referral), and quality of life interventions. The NP will follow up with the patient either in person, by phone, or by videoconferencing at 3 months, at 6 months, and again at 12 months. The NP will be accessing the electronic medical record offered by Alberta Health Services [85] to maintain charting consistency in diagnostic testing, appointments, and communications [85]. During the visits, the NP will check the completion of study questionnaires at the appropriate timepoints, and ask the participant +/− caregiver about the completion of questionnaires. If the NP feels that he/she needs help in managing a participant, he/she will refer the participant back to the community neurologist and/or family physician in charge of the participant at any time throughout the study. As mentioned above, the NP will be sending summaries of visits to the neurologists and family physicians and may ask questions of the community neurologists as to their preferences in treatment approaches as needed (e.g. disease-modifying therapies, treatment of relapses with steroids) in individual situations. This fits within the multidisciplinary model of MS care, seen in MS clinics [11].

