**Methods:**

We will perform a parallel randomized controlled trial. PwMS who are followed by general private-practice neurologists will be randomly assigned to the intervention group (NP-led care) or the ‘usual care’ control group (general neurologist or family physician and registered nurse support). In the intervention group, the NP will assess and provide care to the MS patient and their caregiver at a baseline visit, with 3-month and 6-month follow-up visits. PwMS in the control group will receive usual care provided by their community neurologists or family physicians with the standard assistance provided by registered nurses experienced in MS care. The primary outcome will be the difference in change in the patient’s anxiety and depression scores as measured by the validated Hospital Anxiety and Depression Scale (HADS) questionnaire at 3 months. Secondary outcomes will include difference in change in HADS at 6 months; Modified Fatigue Impact Scale scores (MSIF) at 3 and 6 months; EQ-5D scores at 3 and 6 months; caregiver health-related quality of life in MS measures (CAREQOL-MS) at 3 and 6 months; number of visits and phone calls to healthcare professionals recorded by patient, and satisfaction with NP-led care vs usual care measured by the validated Consultant Satisfaction Questionnaire.

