### Individuals who will perform the interventions

The NP will deliver care to those participants randomized to the NP-led care arm during the 6 months of study duration in addition to participants’ regular healthcare providers, while the participants’ regular community neurologists and family physicians in addition to their registered nurses will deliver care to those participants in the usual care arm. There will be one NP participating in the study. She was hired as a general NP, with no specialized skills in MS. However, before moving into the community neurologist environment, she will be mentored and trained for a 3-month period by the MS clinic NP, who has over 6 years of experience in MS, and MS clinic subspecialist neurologists. All the education resources, treatment approaches, interventions, and referral patterns from the MS clinic will be shared with the NP who will be participating in the study. One of the MS clinic neurologists (primary author of this paper, PS) and the MS clinic NP will be continuing to mentor and support this NP through the study. After training at the MS clinic, the study will start after the NP has worked in the community setting for 1 month. This will allow her to orient herself, to understand community neurologists’ practices and approaches, and amalgamate with what she has learned from the MS clinic. This is being done to ensure that the NP involved in the study is comfortable and supported in her approach to supporting PwMS, and to minimize learning curves or experience effects through the study. An information session for the community neurologists and the NP will be set up prior to initiating the study, outlining the study protocol. There are no specific requirements or training for family physicians or community neurologists to have their patients participate in the study. This will ensure their ‘usual’ practice of how they treat PwMS. The administration of surveys and outcome assessments are being done by EPICORE Centre and sent to participants directly. Therefore, no training needs to be done by the NP, community neurologists, or family physicians in this study.

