There are no methods to ensure fidelity of participants to the intervention arm or control arm. The NP is backed up by the community neurologists during the 6 months that she is leading care for participants in the intervention arm. Therefore, she will be writing reports and summaries to the neurologists and family physicians after seeing participants and may ask questions of the community neurologists as to their preferences in treatment approaches (e.g. disease-modifying therapies, treatment of relapses with steroids) in individual situations. This is within the study outline, as the NP is an add-on to the care team for the patients, and primarily leads an intervention of care for the participants, with regular follow-ups at baseline, 3 months, and 6 months, with as-needed appointments or phone calls in between regular follow-up visits.

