### Control arm (usual care arm)

PwMS who are randomized to the usual care arm (community neurologist or family physician and registered nurses) will be contacted by the NP to be scheduled for an NP appointment at 6 months after study conclusion. Thus, every PwMS is given the opportunity to access NP care after their involvement in the study has concluded. During the 6-month period, patients randomized to the control group will receive usual care from community neurologists or family physicians and MS registered nurses. The care will be delivered according to standard practices, and follow-up visits will be conducted according to the various clinical practices of the neurologists’ or family physicians’ clinics. For those in the usual care arm, the EPICORE Centre’s research team will contact the participant +/− caregiver about the completion of questionnaires at the appropriate timepoints. The participant diary will be collected by the NP when the participant in the usual care arm has finished the study and is offered a follow-up visit with the NP outside of the study. If family physicians wish to have more urgent patient assessments, they will be offered the additional opportunity of referring the patient to a community neurologist or a NP outside of the study if they feel that the patient cannot wait 6 months for MS specialized care; these patients will also be excluded from being involved in the study.

Participants are able to initiate contact with their usual community neurologist and/or family physician in either arm of the study, throughout the study as they need. Participants will continue to be followed by their family physicians and regular community neurologists during the study, in either arm. For those in the NP-led care arm, they will receive additional care by the NP during the 6 months of the study duration.

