A longer-term follow-up will be conducted at 12 months to evaluate the long-term differences of the 6-month intervention in change of the patient-reported outcome measures (HADS, MFIS, EQ5D, and CAREQOL-MS). By then, all participants would have seen the NP, and the goal of the late follow-up would be to see if there was (1) long-term impact of the 6-month NP intervention (from those in the original intervention group), and (2) to check the larger patient number impact of the NP intervention upon those within the control group.

If participants score very low or severe on their scales around anxiety, depression, fatigue, quality of life, and/or their caregivers score as very low on their questionnaire, their community neurologist and/or family physician will be contacted to see the participant on an urgent basis.

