## Limitations

There are study limitations inherent within the process of inviting PwMS to participate in a study looking at alternate ways of delivering care through a NP. This study preferentially selects for individuals who are open to having an NP provide care to them. Additionally, participants are not blinded as to whether they will be in the intervention arm vs the control arm. We will try to address that bias by offering NP visits to every participant in the study—either within 4 to 6 weeks for the intervention arm, or for those in the control arm at 6 months once the study concludes. An additional limitation might be that the NP may initiate appointments and/or phone calls with participants in the intervention arm beyond the three visits outlined in the study protocol where deemed clinically appropriate. We have limited participants to those who speak English and who can attend visits with the NP. This may limit the generalizability of the results with those who live in more rural areas, and those who primarily speak different languages. Finally, we will be relying on participants’ self-reported data to complete patient diaries to record their outpatient interactions with the healthcare system (e.g. family physician and neurologist visits and phone calls) and to complete the questionnaires which could be susceptible to subjective bias. We cannot control all of the healthcare providers that will be accessed by participants in either arm but will keep track of that information through the completion of patient diaries, and the search of Netcare, provincial clinical data records. As well, referral to the appropriate providers for support (i.e. psychologist) is part of the intervention itself when initiated by the NP to improve participants’ depression, anxiety, and quality of life. Since this is being tracked in our study, we may see that part of the NP’s impact upon the participants in the intervention arm is to correctly connect participants with the appropriate support services. Finally, ‘usual care’ amongst similar NP studies and amongst practitioners does vary, a limitation of any study trying to assess interventions above and beyond norms of clinical practice.

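### The protocol article gives two NP follow-up schedules for the intervention arm, one ending at 6 months and one adding 12 months, so the meaning of that arm's 12-month result is unclear

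*Protocol article*

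**What the plan says.** The intervention-arm section has the NP follow up participants in person, "by phone, or by videoconferencing at 3 months, at 6 months, and again at 12 months". It names the three time points in one sentence without distinguishing them, then says that the NP checks questionnaire completion during visits.

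Other sections describe a shorter schedule:

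- The abstract has the NP provide care "at a baseline visit, with 3-month and 6-month follow-up visits".
- The section on individuals who will perform the interventions describes an add-on "with regular follow-ups at baseline, 3 months, and 6 months, with as-needed appointments or phone calls in between regular follow-up visits". It also says that the NP delivers care to "participants randomized to the NP-led care arm during the 6 months of study duration".
- The control-arm section says of NP-arm participants that "they will receive additional care by the NP during the 6 months of the study duration".
- The limitations section discusses NP contacts "beyond the three visits outlined in the study protocol".
- The data collection section places the satisfaction questionnaire at 6 months, when NP care is said to conclude.

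The outcomes section gives the first goal of the 12-month follow-up as the "long-term impact of the 6-month NP intervention (from those in the original intervention group". Twelve months is also named in the first study objective at the end of the background.

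**The concern.** A durability claim needs a defined end of treatment. If NP follow-up stops at month 6, the NP arm's 12-month HADS, MFIS and EQ5D scores describe participants six months after scheduled NP contact ended. If the NP sees or calls them again at month 12, the scores come from around the time of a further contact by the same provider. That contact may include care, and it may prompt questionnaire return.

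The arms could also differ in how responses are prompted: the NP checks completion at visits in the NP arm, while the coordinating centre contacts controls. A reader of the results could not tell which of the two situations the 12-month figures represent.

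**Working it through.** The check is a comparison of text. The plan prints no figure for this point, and it depends on no sample size, power or alpha.

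**Step 1. Count scheduled NP contacts in the intervention arm.**

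| Place in the protocol article | Scheduled NP contacts | Count |
|---|---|---|
| Abstract, Methods | baseline, 3, 6 months | 3 |
| Individuals who will perform the interventions | baseline, 3, 6 months, plus as-needed contacts between them | 3 |
| Limitations | number only | 3 |
| Intervention arm | first consultation, then 3, 6, 12 months | 1 + 3 = 4 |

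The difference is 4 − 3 = 1 scheduled contact, at month 12. The count measures the inconsistency and not the dose of care, because unscheduled appointments and calls are allowed under either schedule.

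**Step 2. Compare the stated end of NP care.** The section on individuals who will perform the interventions and the control-arm section both place NP care within the 6 months of the study. The data collection section treats month 6 as its conclusion. Only the intervention-arm section carries NP follow-up to month 12.

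**Step 3. Establish what the 12-month time point is elsewhere.** Table 1 and the data collection section list questionnaires. The data monitoring section has the coordinating centre send reminders. The section on who delivers the intervention says surveys are administered by that centre and go straight to participants. The trial status section says the 12-month follow-up was sent out. None of these mentions an NP visit, and none excludes one.

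**Step 4. Identify what the text leaves open.** No section says whether the 12-month NP contact is care or a completion check, or whether it falls before or after the 12-month questionnaires. Its effect on the scores therefore cannot be calculated.

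**Step 5. Find which results can be affected.** The primary outcome is at 3 months and the secondary outcomes listed with a time point are at 3 and 6 months, so a contact at month 12 cannot alter them. The 6-month satisfaction score cannot be changed by a later contact either; only the description of its timing conflicts. What remains is the 12-month follow-up in the first objective and the outcomes section. With planned enrolment of 220 split 1:1, 220 / 2 = 110 participants per arm would be due for it before any losses. The 220 already allows for dropout from 200.

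**The case against.** The strongest reply is that the extra time point may be only a study contact. Every other section treats month 12 as questionnaires sent by the coordinating centre, and the intervention-arm section itself gives the NP the task of checking completion. A brief contact for that purpose at month 12 would fit with NP care ending at month 6, and the questionnaire might already be done when the contact takes place. This reading is possible. It is not what the intervention-arm section says, since that section groups month 12 with the 3- and 6-month follow-ups and offers in-person or video contact. The conflict in the text remains, but the reply does limit the consequence.

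A reader might infer more: that the NP arm stayed under NP care for the whole of 12 months, or that its 12-month scores were necessarily collected during renewed care. The documents support neither. At most one scheduled contact is in question, months 6 to 12 hold no other, and its order relative to the questionnaire is not given.

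A second reply also stands. The outcomes section acknowledges that everyone will have seen the NP by month 12, and the section on post-trial care gives controls 6 months of NP care after the study. That crossover limits the between-arm comparison at 12 months whatever the NP-arm schedule was, and removing the inconsistency will not restore a clean comparison. The inconsistency bears on how the NP arm's own 12-month result is described.

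**Conclusion.** The inconsistency is real and lies in the current text: three scheduled NP contacts in three places, four in the section that defines the intervention. The text must say which schedule stands and what the 12-month contact is. Which schedule is right is for the investigators to state.

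The consequence is limited to the 12-month follow-up and to the label put on the NP arm's result there. It would be wrong to infer any threat to the 3-month primary outcome or to the 6-month outcomes. It would also be wrong to treat the 12-month scores as shown to be distorted: the size and direction of any effect depend on the timing and content of a contact that the document does not describe. The conclusion assumes only that an NP follow-up in person, by phone or by video is a contact with the participant.

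The point is worth settling, because the stated 12-month aim presumes an intervention that finished at month 6. The trial status section places final quality assurance and analysis still ahead.

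**What to change.** 1. Reconcile the abstract with the sections on individuals who will perform the interventions, the intervention arm, the control arm, data collection, outcomes and limitations, so that one NP schedule stands. State whether the 12-month NP contact is care or only a check on questionnaire completion.
2. From the charts already kept, tabulate NP contacts after month 6 by arm.
3. Keep all 12-month questionnaires in the analysis.
4. If scheduled NP follow-up ran to month 12, describe the NP-arm result as including a 12-month NP contact and not as the lasting effect of a completed 6-month intervention.
5. If an analysis restricted to questionnaires completed before that contact is wanted, make it a sensitivity analysis only. It selects on an event after randomisation and could drop late responders who replied only when the NP asked. It also does not suit controls: their 6 months of NP care start at about month 6 and so end at about month 6 + 6 = 12.

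The cost is a clarification of wording, slightly more descriptive analysis and possibly a less favourable durability claim.

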### Control arm (usual care arm)

PwMS who are randomized to the usual care arm (community neurologist or family physician and registered nurses) will be contacted by the NP to be scheduled for an NP appointment at 6 months after study conclusion. Thus, every PwMS is given the opportunity to access NP care after their involvement in the study has concluded. During the 6-month period, patients randomized to the control group will receive usual care from community neurologists or family physicians and MS registered nurses. The care will be delivered according to standard practices, and follow-up visits will be conducted according to the various clinical practices of the neurologists’ or family physicians’ clinics. For those in the usual care arm, the EPICORE Centre’s research team will contact the participant +/− caregiver about the completion of questionnaires at the appropriate timepoints. The participant diary will be collected by the NP when the participant in the usual care arm has finished the study and is offered a follow-up visit with the NP outside of the study. If family physicians wish to have more urgent patient assessments, they will be offered the additional opportunity of referring the patient to a community neurologist or a NP outside of the study if they feel that the patient cannot wait 6 months for MS specialized care; these patients will also be excluded from being involved in the study.

Participants are able to initiate contact with their usual community neurologist and/or family physician in either arm of the study, throughout the study as they need. Participants will continue to be followed by their family physicians and regular community neurologists during the study, in either arm. For those in the NP-led care arm, they will receive additional care by the NP during the 6 months of the study duration.

### Outcomes

The primary outcome will be the difference in change in the HADS: depression score (HADS-D) and HADS anxiety score (HADS-A) between intervention and control groups at 3 months [74].

Secondary outcomes include difference in change in (a) HADS-D and HADS-A scores at 6 months; (b) EQ5D at 3 and 6 months [23], a scale used by Alberta Health Services to measure impact of healthcare delivery models; (c) MFIS score at 3 and 6 months [82], a severely disabling symptom commonly experienced by those living with MS; (d) CAREQOL-MS, a caregiver quality of life questionnaire for those informal caregivers helping PwMS who can experience burden and lack of support, at 3 months and 6 months [83], participant diary of outpatient healthcare interactions during the study period and provincial database search for inpatient/emergency admissions, to see if the intervention of a NP decreases other costs of healthcare providers in the care of PwMS; in addition to (e) a CSQ at 6 months [84], to see if participants perceive NP-led care to be equivalent to that provided by their usual care (community neurologist, family physician, and registered nurse). We are measuring the impact of these secondary outcomes and comparing outcomes as change from baseline in both the intervention and control arms, to see if any of these secondary outcome measures change as a result of an NP being involved in care. Individual sociodemographic factors such as age (generated from date of birth) for descriptive statistics and addresses will be obtained for mailing purposes throughout the study, as we may have to mail follow-up questionnaires and contact patients for follow-up. Other identifying information such as healthcare number will be collected to gather data for secondary outcomes such as admission to hospital and/or emergency visits, MS relapse, infection, or adverse events from medication. Patients will complete diaries of phone calls and visits to GP, neurologist, emergencies, healthlink (online Alberta health services phone support), and other healthcare professionals such as physiotherapists, occupational therapists, pharmacists, dieticians, homecare, and social workers. This information will be de-identified once collected. These secondary outcome measures will be explored and compared between intervention and control arms.

A longer-term follow-up will be conducted at 12 months to evaluate the long-term differences of the 6-month intervention in change of the patient-reported outcome measures (HADS, MFIS, EQ5D, and CAREQOL-MS). By then, all participants would have seen the NP, and the goal of the late follow-up would be to see if there was (1) long-term impact of the 6-month NP intervention (from those in the original intervention group), and (2) to check the larger patient number impact of the NP intervention upon those within the control group.

If participants score very low or severe on their scales around anxiety, depression, fatigue, quality of life, and/or their caregivers score as very low on their questionnaire, their community neurologist and/or family physician will be contacted to see the participant on an urgent basis.

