### Sample size and power analysis

Honarmand and Feinstein (2009) [74], validated the use of HADS in PwMS [Baseline scores and standard deviation (SD)]. Using the validation information in the study by Honarmand and Feinstein and the following assumptions of 80% power and a two-sided alpha of 0.05, a total sample size of 200 (100 in each group) will be required to detect 1.5 difference [86], between the intervention and the control groups. The same size has been calculated for both HADS-A and HADS-D. This study will use the sample size calculated for HADS-A, as it required a larger sample size and to ensure there will be sufficient power for both HADS-A and HADS-D. This sample size will be inflated to 220 to account for possible dropouts, losses to follow-up, and withdrawals of consent.

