### Statistical analysis

Data analysis will be performed using the computer R 3.4.0 software (Vienna, Austria; https://www.R-project.org/) and SAS 9.4 software (SAS Institute Inc. Cary, NC, USA). Patient demographic and clinical characteristics will be analysed using descriptive statistics.

The primary outcome of difference in change of HADS-D and HADS-A from baseline to 3 months between the intervention and control, will be tested using an independent *T*-test. The last observation will be carried forward in the case of missing data. Secondary outcomes will be analysed using the same methods as described below. The CSQ will be treated as continuous variables with an overall satisfaction score as a sum of the sub-scales for each question in the CSQ.

Categorical variables will be reported using frequency and percentage and continuous variables will be reported using mean (SD) or median [interquartile range (IQR)] as appropriate. Univariable analysis will be conducted to determine if there is a statistical significance between the outcomes (e.g. baseline to 3 months and 6 months, respectively). Chi-square and independent *T*-tests will be used for the univariate analysis, or where appropriate the non-parametric tests (Fishers test and Wilcoxon rank test). ANOVA and generalized linear models will be used to test for overall differences between the intervention and control at the different timepoints and variances amongst the variables by group and timepoints. Post hoc Tukey HSD (Honestly Significant Difference) test will be performed afterwards with adjustments made using the Bonferroni method. All test assumptions will be checked during the data analysis process. Statistical significance will be set at *p* values less than 0.05. In the case of missing data, we will utilize the last value carried forward method to impute missing values.

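### HADS-D and HADS-A are both primary and each is tested at 0.05, but no rule says whether one or both must be significant, so either the 5% error rate or the 80% power does not hold for the trial's conclusion

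*Protocol article*

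**What the plan says.** Under Outcomes, the protocol article defines the primary outcome through two separate subscale scores: "The primary outcome will be the difference in change in the HADS: depression score (HADS-D) and HADS anxiety score (HADS-A"), compared between arms at 3 months. It does not use a HADS total or a composite.

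Under Statistical analysis, "The primary outcome of difference in change of HADS-D and HADS-A from baseline to 3 months between the intervention and control" is tested with an independent t-test. The threshold is the same for everything: "Statistical significance will be set at *p* values less than 0.05".

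Under Sample size and power analysis, each subscale is sized separately with "80% power and a two-sided alpha of 0.05" for a 1.5-point difference. The larger requirement, that for HADS-A, is adopted "to ensure there will be sufficient power for both HADS-A and HADS-D". This gives 100 per arm, raised to 220 in total for losses.

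The only multiplicity correction in the article concerns comparisons made after an ANOVA or generalized linear model across groups and timepoints: "Post hoc Tukey HSD (Honestly Significant Difference) test will be performed afterwards with adjustments made using the Bonferroni method".

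The hypothesis at the end of the Background names depression and anxiety together, without making that a success criterion.

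**The concern.** A trial with two primary tests needs a sentence saying what counts as success, and this article has none. Suppose one subscale reaches p<0.05 and the other does not. The article cannot then say whether the trial was positive, and the choice could be made after the results are seen.

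The stated figures do not fit either choice. If one significant subscale is enough, two tests at 0.05 carry a family-wise error above 5%. If both are needed, the 80% in the sample size section belongs to one test and not to the conclusion.

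The article does fix a multiplicity method, but attaches it to post hoc contrasts and not to the two primary tests. There, two family-wise procedures are stacked on each other.

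**Working it through.** **Inputs from the article.** Two primary subscales (Outcomes); t-tests judged at 0.05 (Statistical analysis); two-sided alpha 0.05, power 80%, difference 1.5, 100 per arm (Sample size and power analysis).

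**Inputs not in the article.** The SD is not stated; a validation study is cited for it. The correlation between the two test statistics is not given either, so a range of 0 to 0.9 is shown.

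**1. The plan's own figure.** Without an SD, the 100 per arm cannot be reproduced independently, so the SD is back-solved with the normal approximation:

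SD = 1.5 / [(1.960 + 0.842) × √(2/100)] = 1.5 / (2.802 × 0.1414) ≈ 3.79.

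This SD belongs to HADS-A, which set the sample size. HADS-D needed fewer patients, so its power at 100 per arm exceeds 80% by an amount the article does not give.

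**2. If either subscale suffices.** With independent tests, the family-wise error is 1 − 0.95² = 0.0975. With correlated tests it is 1 − P(|Z1| < 1.96 and |Z2| < 1.96) under a bivariate normal distribution.

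**3. If both are required.** The error rate is at most 0.05. Joint power is P(both significant). With each subscale at 80% and independence, it is 0.80 × 0.80 = 0.64; correlation raises it.

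| Assumed correlation | Family-wise error, either suffices | Joint power, both required, each at 80% |
|---|---|---|
| 0 | 9.75% | 64.0% |
| 0.5 | 9.1% | 68.7% |
| 0.7 | 8.3% | 71.3% |
| 0.9 | 7.0% | 75.0% |

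The last column is a floor, because it gives HADS-D only 80%. As an illustration, if HADS-D had 90% power, joint power would be 0.80 × 0.90 = 72% at correlation 0 and about 77% at 0.7.

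**4. Power under an either-subscale rule that keeps 5%.** Holm's procedure tests the smaller p-value at 0.025 and, if that is significant, the other at 0.05. Any subscale with p<0.025 is always declared significant, so per-subscale power is at least the power at 0.025. The critical value is 2.241, and Φ(2.802 − 2.241) = Φ(0.56) ≈ 0.71. Testing both at a flat 0.025 gives a family-wise error of 4.9% at correlation 0 and 4.3% at 0.7. Keeping 80% power at 0.025 would take 2 × (2.241 + 0.842)² × 3.79² / 1.5², about 122 per arm or 244 in total before losses. Recruitment is reported as complete, so this only shows what the alpha split costs.

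**5. The post hoc step.** Tukey HSD already controls the family-wise error over all pairwise contrasts in its family. A Bonferroni adjustment of the same contrasts corrects them a second time. The resulting power loss depends on how many contrasts are in the family, which the article does not state, so no figure is attached here.

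**The case against.** The strongest reply is that the text leans towards requiring both. The Outcomes section speaks of one primary outcome, the hypothesis pairs depression with anxiety, and the sample size is chosen with both subscales in view. Under that rule the error rate does not rise at all. This stands as far as it goes: the wording is compatible with a both-required rule. But no section states it as a rule, and if it were the rule, the 80% would not describe the chance of success.

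A reader might infer that the false-positive rate is simply doubled. The article does not support that. The inflation arises only if either subscale counts, and 9.75% is the value under independence. Two subscales of one questionnaire in the same patients are likely to be positively correlated, which lowers it.

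A reader might also infer that the sample size section overclaims joint power. It does not. Taking the larger of two requirements gives adequate power for each subscale, which is the natural sense of "to ensure there will be sufficient power for both HADS-A and HADS-D".

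A third tempting reading is that the Tukey and Bonferroni step makes the 3- and 6-month differences almost undetectable. It does not gate them. The primary outcome has its own t-test, and the secondary outcomes are assigned the same methods. The Bonferroni wording might also refer to adjustment across outcomes rather than across the Tukey contrasts.

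Finally, a success rule is something that a statistical analysis plan, not shown here, often carries. That would excuse silence. But this article itself fixes two primaries, their test, the 0.05 threshold and a multiplicity method that leaves those two tests out.

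**Conclusion.** The point holds in conditional form. As written, two primary tests at 0.05 have no success rule and no adjustment. An either-subscale claim carries a family-wise error of 7.0–9.75% over assumed correlations of 0.9 down to 0. A both-required claim keeps 5%, but has joint power of at least about 64–71% over correlations of 0–0.7 and not 80%; the true figure is somewhat higher because HADS-D needed fewer patients.

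The error rates rest only on the assumed correlation. The power figures also assume a true 1.5-point difference on both subscales and the 80% design power, which for HADS-A corresponds to the back-solved SD of about 3.79.

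The doubled correction in the post hoc step is a separate, smaller fault. It does not affect the primary t-tests.

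**What to change.** Before the final analysis, add the success rule to Outcomes and Statistical analysis. Either of these would do:

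- **Either subscale, with Holm's procedure:** the smaller p-value is tested at 0.025 and, if significant, the other at 0.05.
- **Both required:** each subscale is tested at 0.05, with no alpha split.

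Then restate the power in the sample size section for the chosen rule. For Holm this is at least about 71% per subscale at 100 per arm for 1.5 points, with the SD written out. For both required, it is the joint power over a stated range of correlations.

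Trial status says that final analysis has not begun, so the rule can still be set in advance of it. Data monitoring also plans an interim analysis after the 3-month follow-up, so the change should be dated and should record whether 3-month results by arm had been seen.

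Separately, under Statistical analysis, remove the Bonferroni layer on top of Tukey HSD and report the pre-specified arm differences at 3 and 6 months with confidence intervals.

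The cost is wording and a less favourable power statement, per subscale or joint. No patients or data are added.
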